## Abstract

**Background:**

Fibrotic interstitial lung diseases (ILDs) are chronic and often progressive conditions resulting in substantial morbidity and mortality. Shortness of breath, a symptom often linked to oxygen desaturation on exertion, is tightly linked to worsening quality of life in these patients. Although ambulatory oxygen is used empirically in their treatment, there are no ILD-specific guidelines on its use. To our knowledge, no studies are available on the effects of ambulatory oxygen on day-to-day life in patients with ILD.

**Methods/design:**

Ambulatory oxygen in fibrotic lung disease (AmbOx) is a multicentre, randomised controlled crossover trial (RCT) funded by the Research for Patient Benefit Programme of the National Institute for Health Research. The trial will compare ambulatory oxygen used during daily activities with no ambulatory oxygen in patients with fibrotic lung disease whose oxygen saturation (SaO_2_) is ≥94% at rest, but drops to ≤88% on a 6-min Walk Test. The randomised controlled trial (RCT) will evaluate the effects on health status (measured by the King’s Brief ILD Questionnaire: K-BILD) of ambulatory oxygen used at home, at an optimal flow rate determined by titration at screening visit, and administered for a 2-week period, compared to 2 weeks off oxygen. Key secondary outcomes will include breathlessness on activity scores, as measured by the University of California San Diego Shortness of Breath Questionnaire, global patient assessment of change scores, as well as quality of life scores (St George’s Respiratory Questionnaire), anxiety and depression scores (Hospital Anxiety and Depression Scale), activity markers measured by SenseWear Armbands, pulse oximetry measurements, patient-reported daily activities, patient- and oxygen company-reported oxygen cylinder use. The study also includes a qualitative component and will explore in interviews patients’ experiences of the use of a portable oxygen supply and trial participation in a subgroup of 20 patients and carers.

**Discussion:**

This is the first RCT of the effects of ambulatory oxygen during daily life on health status and breathlessness in fibrotic lung disease. The results generated should provide the basis for setting up ILD-specific guidelines for the use of ambulatory oxygen.

**Trial registration:**

National Clinical Trials Registry, identifier: NCT02286063. Registered on 8 October 2014 (retrospectively registered).

**Electronic supplementary material:**

The online version of this article (doi:10.1186/s13063-017-1912-9) contains supplementary material, which is available to authorized users.

## Background

The hallmark symptom of fibrotic interstitial lung diseases (ILD) is breathlessness, which progressively limits the ability of patients to carry out routine activities and ultimately can affect their independence. Breathlessness is the main determinant of quality of life in patients with idiopathic pulmonary fibrosis (IPF), the most common of the idiopathic ILDs [1]. Fibrotic lung diseases profoundly affect an individual’s sense of wellbeing, with anxiety, depression and fatigue often accompanying exertional limitation, leading to a loss of health status. With limited pharmacological therapy proven to prolong survival in many ILDs, attempts to improve or maintain health status are of crucial importance.

Breathlessness on exertion, formally measured by the 6-min Walk Test (6MWT) [2], is often associated with a fall in oxygen saturation (SaO_2_), which in ILD patients can be particularly marked [3–6]. The 6MWT is a widely used field test measuring functional exercise capacity, repeatedly observed to have good validity as a functional and prognostic marker in IPF [7, 8]. Ambulatory oxygen used during a 6MWT or bicycle endurance test has been reported to improve breathlessness, distance walked, and breathlessness recovery time [9, 10]. Frank and coauthors reported that further up-titration of ambulatory oxygen in order to maintain saturation values above 90% and/or reaching a 6-L/min flow rate during a 6MWT seemed to improve exercise capacity in IPF, as measured by a 6MWT, even in patients already using oxygen at home [11]. However, two studies have failed to report a significant benefit on distance walked or dyspnoea of supplemental oxygen on either the 6MWT [12] or a shuttle endurance test [13], possibly because neither adequately titrated oxygen requirements to appropriately correct the patient’s exertional desaturation, as suggested in a recent Cochrane review [14].

Although a number of chest physicians prescribe ambulatory oxygen to ILD patients with desaturation on exercise, there are no nationally recognised guidelines to direct ambulatory oxygen prescription. In particular, NICE guidelines for oxygen use only address chronic obstructive pulmonary disease (COPD): (http://guidance.nice.org.uk/CG101), a disease which markedly differs from IPF or other ILDs. The recent British Thoracic Society (BTS) oxygen guidelines only briefly touch on ambulatory oxygen and give no specific guidance on its use in ILD, indeed recommending against its use in most cases [15]. Specifically, there are no published studies investigating the effects of ambulatory oxygen on day-to-day life in patients with fibrotic ILD, or assessing whether oxygen-induced improvements in 6MWT performance predict response to supplemental oxygen during activities of daily living, and an overall improvement in health status.

We have, therefore, planned a prospective study to assess whether individuals with fibrotic ILD whose SaO_2_ falls to ≤88% on a 6MWT, but are not hypoxic at rest, benefit from the use of ambulatory oxygen in their daily lives, by assessing changes in health status. The proposed project is the first of its kind in ILD, and addresses an under-researched area in urgent need of study. The study has the potential to lead to significant advances in the treatment and the understanding of exercise limitation in patients with ILD, and will represent an essential step towards the development of guidelines on oxygen use in ILD.

### Objectives

The main aim of this project is to establish whether ambulatory oxygen in patients with fibrotic ILD whose oxygen saturation falls to ≤88% on a 6MWT, leads to a significant improvement in health status, as measured by the King’s Brief Interstitial Lung Disease Questionnaire (K-BILD) [16]. Key additional outcomes will be the evaluation of dyspnoea during activities of daily living as measured by the University of California San Diego Shortness of Breath Questionnaire (UCSD SOBQ) [17], as well as the global patient assessment of change [18]. Further secondary outcomes will include monitored (SenseWear Armbands) and patient-recorded activity parameters, as well as quality of life scores assessed by the St. George’s Respiratory Questionnaire (SGRQ) [19] and the Hospital Anxiety and Depression Scale (HADS) [20]. We also aim to assess whether the improvement in 6MWT performance induced by portable oxygen can predict benefit of ambulatory oxygen in day-to-day living, by a placebo air-controlled 6MWT performed at the start of the study, to assess changes to the 6MWT parameters induced by supplemental oxygen. An economic evaluation will assess the potential value for money provided by ambulatory oxygen by comparing the health system costs and health-related benefits to those of no ambulatory oxygen.

In addition, qualitative semistructured interviews at the end of the 4-week period in a subgroup of 20 patients will be conducted to evaluate patients’ and carers’ experiences regarding the use of ambulatory oxygen and trial participation.

## Methods/design

The AmbOx study is a UK, multicentre, prospective, randomised controlled crossover trial of ambulatory oxygen against no ambulatory oxygen over a 4-week period (2 weeks on ambulatory oxygen and 2 weeks on no portable oxygen), to evaluate the effects of ambulatory oxygen on health status in patients with ILD. Patients whose SaO_2_ at rest is ≥94% will be screened by performing a 6MWT as part of their routine clinical assessment in order to identify those patients whose SaO_2_ drops to ≤88%. In those who desaturate below this threshold, a further 6MWT will be conducted with titration of oxygen flow so that for least half of the 6MWT, oxygen saturation with supplemental oxygen is maintained at >90% (for more detailed information on oxygen titration, see section 10.2 of the protocol (Additional file 1).

Following consent to the study, patients meeting eligibility criteria and deemed clinically stable at the end of the 2-week run-in period, and not expecting to require any change in their background medication, will be assigned in random order to 2 weeks on ambulatory oxygen or no oxygen during the baseline visit. Optimal oxygen flow rates will be determined during the screening visit on the basis of the entry 6MWT on oxygen, as detailed above. At the start of the active part of the trial, the effects of ambulatory oxygen on 6MWT performance will be formally evaluated by performing two 6MWTs, one on oxygen and one on placebo air-filled canisters, at the flow rate identified during the screening visit, in random order, with a rest of at least 30 min between tests. The patient will be blind to the content of the canisters. Measured parameters will include 6MWT distance, oxygen saturation and heart rate measured continuously (WristOx2™ model 3150), Borg Dyspnoea and Fatigue Score [21] before and at the end of the test, time to recovery of heart rate, and oxygen saturation. These parameters will be related to changes in the primary and secondary outcome variables as detailed in subsequent sections, to identify any baseline predictors of responsiveness. Two different randomisation lists, independent of each other, will, therefore, be used. One randomisation list will determine the order of placebo air versus oxygen-filled canisters for the placebo-controlled 6MWT occurring at the baseline visit, the other randomisation list will determine the order of oxygen versus no intervention for the 4-week trial.

Following completion of the 2 weeks on the treatment arm assigned during the baseline visit (ambulatory oxygen or no intervention), patients will cross over to receive the alternative treatment for a further 2 weeks. The study design is outlined in Additional file 2: Figure S1. More details are available in the AmbOx protocol, version 3.0, dated 1 December 2014 (Additional file 1).

### Location and setting

AmbOx is sponsored by the Royal Brompton and Harefield NHS Foundation Trust and will recruit subjects from three UK centres (RBH; Aintree University Hospital led by [name]; Bristol ILD Unit led by HA), all with expertise in ILD.

### Study population and eligibility criteria

A total of 80 subjects will be enrolled and randomised. Subjects should fulfil the following criteria:A diagnosis of fibrotic lung disease, including idiopathic pulmonary fibrosis, fibrotic nonspecific interstitial pneumonia, fibrotic hypersensitivity pneumonitis, fibrotic organising pneumonia and nonclassifiable fibrotic ILD. Patients with fibrotic sarcoidosis or connective tissue disease (CTD)-associated fibrotic ILD will be included provided that there is no significant musculoskeletal involvementPatients whose oxygen saturation (SaO_2_) at rest on room air is ≥94% and falls to ≤88% on a baseline 6MWTPatients with stable symptoms (no changes in medications and no chest infections) and treatment during the period of 4 weeks prior to being randomised into the study, including the 2-week run-in periodPatients able to provide written informed consent

The Patient Information Sheet and Informed Consent Form can be found in Additional files 3 and 4, respectively. Subjects should not enter the study if any of the exclusion criteria listed in Additional file 5 are present. Patient will have had an echocardiogram and spirometry performed within 6 months prior to the screening visit or within 6 weeks following this. Serum brain natriuretic peptide (BNP) levels will be collected for all patients within a month from the screening visit.

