### Explanatory outcome measures

Benefit of ambulatory oxygen in relation to the following:o Improvement in baseline 6MWT performance on oxygen (at the flow determined during the screening visit) compared to placebo airo Outcome in relation to underlying ILD diagnosis: IPF versus non-IPFo Outcome in relation to the presence of pulmonary vascular disease/pulmonary hypertension (PH), defined on the basis of baseline echocardiogram (right ventricular systolic pressure (RVSP) >40 mmHg and/or right ventricular (RV) dilatation/reduced function) and/or elevated baseline serum BNP levels

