### Blood samples

Blood samples will be taken at the start of the 4-week period to evaluate serum BNP levels. All BNP measurements will be performed in the same laboratory at the RBH.

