### Statistical analysis

Before starting the data analysis, the level and pattern of the missing data in the baseline variables and outcomes will be established by forming appropriate tables. The likely causes of any missing data will be investigated. This information will be used to determine whether the level and type of missing data have the potential to introduce bias into the analysis results for the proposed statistical methods, or to substantially reduce the precision of estimates related to treatment effects.

The potential effects of performance, attrition and evaluation bias associated with the lack of a placebo arm will be considered. Although we are not able to fully exclude bias in the patient-reported outcomes, this will be minimised by exploring correlations between the primary endpoint and secondary outcomes, including analysis of SenseWear Armband activity monitors, to assess the possibility that a placebo effect is associated with evaluation bias. Attrition bias should be minimised by the fact that there will be no change in dosing for the duration of the trial, and we do not expect there to be any toxicity from the use of ambulatory oxygen. Subjects will be withdrawn from the trial only if they wish to do so or because of disease progression and the development of hypoxia at rest. We do not expect there to be any bias in the background provision of care (performance bias) depending on use or not of oxygen, as patients enrolled into the trial will be those not expected to change their treatment for the duration of the study.

Although we will not adjust for baseline K-BILD score in the primary analysis, secondary analyses using the K-BILD filled in at baseline visit (week 0) as a covariate, or mean of the K-BILD score at screening visit (week −2) and at baseline visit (week 0) will be considered.

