### Primary outcome measure

The primary outcome will be the difference in K-BILD score on oxygen compared to no oxygen. We will use a generalised linear model with the difference in health status as the independent variable and treatment sequence as a covariate. If the assumption of the mixed model is not met, data will be either log-transformed and/or other nonparametric methods will be considered. Any adjusted analyses will be performed as secondary sensitivity analysis including adjusting for any covariate that is itself linked to the primary outcome (see below)Analysis of the primary outcome will be by intention-to-treat. The data will be analysed according to the initial randomisation groups irrespective of subsequent withdrawals. However, should there be a sizeable frequency of protocol variation, per protocol analysis will also be performedThe hypothesis to be tested is that ambulatory oxygen improves health status compared to no treatment. The study will be considered positive if statistical significance at the level of 0.05 (two-tailed) is achievedo Sensitivity analyses will include adjustment for any covariates linked to the primary outcome. These may include baseline K-BILD measurement, age, gender, smoking history, Body Mass Index (BMI), ILD severity as measured by the Composite Physiologic Index (CPI), presence of PH as measured by echo, baseline BNP levels, etc.o Patient-reported consumption of oxygen cylinders will also be factored in as a covariate. Its validity will be checked against oxygen company-reported cylinder consumption wherever possible, and, in a subgroup of patients, by direct observation by clinical nurse specialist (CNS) home visits (Aintree centre)o To assess the relationship between the response to supplemental oxygen measured with a series of parameters during the placebo air versus oxygen 6MWT and the benefit seen in day-to-day life with ambulatory oxygen, to identify any baseline predictors of responsiveness. These parameters will be included in the statistical model as fixed- effect variables. Possible 6MWT predictors to be analysed will include area under the curve of oxygen saturation, walked distance, maximum/minimum and mean heart rate, end-test dyspnoea, end-test oxygen saturation, end-test heart rate, and recovery times to baseline dyspnoea, heart rate and saturationo Exploratory sensitivity analyses of the effects of ambulatory oxygen will be conducted in predefined subgroups, including:

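### The echocardiogram and spirometry used as baseline measures may be done as late as the week-4 final visit

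*Protocol article*

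**What the plan says.** All places are in the protocol article.

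- **Test window** (Study population and eligibility criteria): every patient will have had an "echocardiogram and spirometry performed within 6 months prior to the screening visit or within 6 weeks following this".
- **Schedule**: the Statistical analysis section puts screening at week −2 and baseline at week 0. This agrees with Methods/design, where patients are "deemed clinically stable at the end of the 2-week run-in period". Assignment of interventions places randomisation at the baseline visit. Data collection and management puts the crossover visit two weeks after baseline and the final visit at four weeks.
- **Use of the echocardiogram**: Explanatory outcome measures has PH "defined on the basis of baseline echocardiogram" and/or a raised baseline BNP.
- **Use as covariates and subgroup** (Primary outcome measure, under Statistical analysis): candidate covariates for the sensitivity analyses include the Composite Physiologic Index (CPI), "presence of PH as measured by echo, baseline BNP levels". Patients with and without PH form a predefined exploratory subgroup.
- **BNP timing**: the eligibility section says "Serum brain natriuretic peptide (BNP) levels will be collected for all patients within a month from the screening visit". The Blood samples section says "Blood samples will be taken at the start of the 4-week period to evaluate serum BNP levels".

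**The concern.** A baseline effect modifier should be fixed before treatment can influence it. The stated window allows the echocardiogram, and the spirometry, to be done at any time up to the end of follow-up. Nothing in the article as shown requires either test before randomisation.

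Three consequences follow for the PH and severity analyses:

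- A value taken after the oxygen fortnight may carry any effect that oxygen has on it.
- A value taken after a deterioration may reflect the outcome rather than predict it. The article lists disease progression and lower respiratory tract infection among expected events.
- In a crossover, an echocardiogram at week 2 follows oxygen in one sequence and precedes it in the other, so its relation to exposure depends on the randomised order.

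A patient who withdraws before a late test may also have no PH status, so missing classification could depend on the course after randomisation. The Discussion section names predictors of benefit, and characteristics of non-responders, as things the trial should show, and PH is one of three modifiers listed under Explanatory outcome measures.

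**Working it through.** **Timeline, counting screening as day 0**

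| Event | Nominal week | Day |
|---|---|---|
| Screening | −2 | 0 |
| Baseline and randomisation | 0 | 14 |
| Crossover visit | 2 | 28 |
| Final visit | 4 | 42 |

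**Echocardiogram and spirometry**

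1. Latest permitted day = 6 × 7 = 42, which is the day of the final visit.
2. Days after randomisation at that point = 42 − 14 = 28. A patient who has followed the schedule has by then completed the oxygen fortnight, whichever order was assigned.
3. Share of the post-screening window that follows randomisation = 28/42 = 67%.
4. Share of the whole window, taking six months as about 26 weeks = 4/(26 + 6) = 4/32 = 12.5%.
5. Sensitivity to the run-in length: with a run-in of r weeks the window closes 6 − r weeks after randomisation. At the stated r = 2 this is 4 weeks. The window would close by randomisation only if r were 6 or more.

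Steps 3 and 4 describe the permitted calendar. Neither says how many patients would use the late part.

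**BNP**

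1. Under the Blood samples section, the sample is at week 0, day 14, before home oxygen.
2. Under the eligibility section read alone, and only if the month runs forward from screening, the latest day is 28 to 31. That is 14 to 17 days after randomisation and 0 to 3 days after the crossover visit.
3. Day 14 lies inside a month of screening, so one week-0 sample satisfies both sections.

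**Does the planned size depend on any of this?** No. Taking the stated SD of 20 as that of the within-patient difference (an assumption), a difference of 8, two-sided 5% significance and 90% power, a paired t-test needs 68 patients (power 0.902). Then 68/(1 − 0.15) = 80, the planned number. None of these inputs involves PH, CPI, spirometry or BNP.

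**The case against.** The strongest reply has five parts.

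- **BNP.** A reader might infer that the two BNP statements contradict each other, or that the plan permits sampling after oxygen exposure. The documents do not support this. The Blood samples section narrows a looser window, both can be met together, and the analysis sections call the value baseline. This objection stands in full.
- **Mechanism.** A reader might infer that two weeks of ambulatory oxygen would distort these measures. The article gives no figure for such a shift. Its Health economics section expects no short-term effect on disease progression, patients must be stable for four weeks before randomisation, and echocardiograms up to six months old are accepted. This stands against any claim of demonstrated bias. It does not make a week-4 value a baseline value.
- **Design.** Each completer serves as their own control and has one PH label, so a late echocardiogram cannot unbalance the treatment arms. That stands. Misclassification of a modifier, possibly linked to the course during the trial, remains.
- **Weight.** The primary analysis uses none of these variables. They are optional covariates in sensitivity analyses and an exploratory subgroup. This stands and sets the severity.
- **Material not shown.** The Schedule of Events figure and the full protocol may set tighter timing. That limits confidence about practice. The article nevertheless states an explicit window that does not fit its own use of the result, so this is more than a detail left to the analysis plan.

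**Conclusion.** The point holds for the echocardiogram and spirometry, as a minor one. On the nominal schedule the permitted window closes at the final visit, 28 days after randomisation, while the analysis treats the results as baseline. The PH subgroup and the analyses adjusted for PH or severity would then not be strictly baseline.

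The conclusion rests on the nominal visit weeks and on there being no tighter rule in the material not shown. For spirometry it also assumes that CPI is built at least partly from it, which the article does not say.

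Two further inferences would go too far. The 67% does not mean that two thirds of patients are measured late: the share of patients is not given, and those with a qualifying earlier test need no later one. Nor is the trial's main result at risk, since the primary estimate, the significance rule and the sample size of 80 do not use these variables. For BNP there is loose wording to tidy, not a conflict.

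**What to change.** - **New patients:** require the echocardiogram and spirometry on or before the baseline visit, before randomisation. The two-week run-in provides a slot for anyone without a result from the preceding six months.
- **Patients already enrolled** (recruitment began in August 2014): define the PH subgroup and the PH and CPI covariates from values dated on or before randomisation. Repeat the analysis with later values included, as a sensitivity check, because patients without a recent echocardiogram may not be a random subset.
- **BNP:** tighten the eligibility wording so that it gives the week-0 timing already in the Blood samples section.

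The cost is some scheduling of tests that are already required, and a date filter in the analysis. A few patients may be left unclassified in an exploratory subgroup. The primary analysis and the sample size do not change.
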